## Abstract

**Background:**

Depression is the principal cause of disability in the world. High prevalence rates of depression in general populations and college students have been found worldwide and in various cultural groups. Low-intensity cognitive behavioural internet-delivered treatment has demonstrated efficacy in high-income-countries (HICs). However little is known of their potential for adaptation and efficacy in low and middle-income countries.

**Methods:**

Study (1) involves the cultural adaptation of the *Space from Depression* cognitive-behaviour internet-delivered programme with an asynchronous support for depressive symptoms. This includes initial researcher/clinician adaptation and the integration of cultural assessment feedback of the programme by a panel of experts and users through the theoretically-based Cultural Relevance Questionnaire (CRQ). Study (2) describes the implementation of the culturally adapted intervention using a randomised controlled trial methodology. The efficacy trial will include an active treatment group and a waiting-list control group of participants meeting eligibility criteria (mild to moderate depression symptoms). The active condition will consist of 7 weekly modules of internet-delivered cognitive behavioural therapy (iCBT) *Space from Depression*, with post-session feedback support. The primary outcome will be the Patient Health Questionnaire (PHQ-9). The study also involves collection of client reported significant events and client satisfaction with the internet-delivered treatment. Data will be collected at baseline and at post-treatment (week 7), and at follow-up (week 20/3 months). Analysis will be conducted on the intention-to-treat basis.

**Discussion:**

The study seeks to establish a theoretically robust methodology for culturally adapting internet-delivered interventions for mental health disorders and to evaluate the efficacy of a culturally adapted internet-delivered treatment for depression in Colombia, with support. The study will be a first contribution to a method for culturally adapting internet-delivered interventions and also a first to examine the efficacy of such an adapted intervention in Latin America.

**Trial registration:**

Clinical trials NCT03062215. Retrospectively registered 14th February 2017.

## Background

High rates of depression have been reported throughout the world [1, 2]. For instance, a 12-month prevalence rate has been estimated in the U.S. at 9.5% and in Europe at 8.5% of the population [3, 4]. In Colombia, 12-month prevalence is between 6.2% and 12.1% [5–8]. The Colombian National Mental Health Survey (2015) has estimated point prevalence of mild to moderate depressive symptoms at 15.6% and severe depressive symptoms at 4.2% of adults. About 50% of the population does not have access to health services [9], while the majority of the population with mental health problems do not have adequate insurance coverage [10].

Despite the necessity to implement psychological interventions in Latin America, there are few studies in this field [11]. More so, treatments are mostly pharmacological, and evidence-based psychological treatments are rarely used. Furthermore, treatments in low and middle income countries (LMICs) are implemented without considering cultural context: very little research has investigated culturally adapted treatments [12], while there is even less research about internet-delivered treatments [13]. Internet delivered psychological treatment may be a suitable alternative to make evidence-based treatments available, especially when nearly 54% of the population use the internet [14].

### Depressive symptoms in college students

Depressive disorders have shown to be more frequent among college students in comparison with the general population [15]. For instance, a systematic review shows a weighted mean prevalence of depression symptoms in college students of 30.6% [16]. These rates are comparable to reports from Latin America [17–20]. In Colombia one study reported high prevalence of depression symptoms (30%) in students [21]. Another recent study showed 36.2% prevalence of depression symptoms in a university sample [22].

Several variables have been associated with vulnerability of college students to depression: changes in lifestyle related to poor sleep habits, eating disorders, economic stressors and family problems [16, 23]. In spite of the high rates of depression within the college population, research studies and treatment for depression in Colombia have received little attention [24]. Recently, a World Mental Health survey reports that only 16.4% of students received treatment for their mental disorder, while in lower-middle/low income countries it was 6.7% [25].

### Treating depression

Psychological treatments for depression have shown better outcomes in comparison with waiting list or placebo and combined treatment is more effective than pharmacotherapy alone [26, 27]. Boumparis, Karyotaki [28] found that psychological treatments can enhance positive affect and decrease negative affect in depression, contributing to better outcomes. A recent meta-analysis showed that Cognitive Behaviour Therapy (CBT) has been extensively researched and it has been demonstrated to be effective for depression [29].

### Low intensity internet-delivered treatment

Low-intensity internet-delivered treatment involves self-guidance, where the content, including CBT techniques that are typically used in face-to-face therapy are delivered using text, pictures, animations, audio files and videos. This type of intervention is highly structured, it involves psychoeducation, activities and supplementary resources, such as a supporter contact via asynchronous message [30].

Internet-delivered interventions have an established empirical base for major depression [31], sub-threshold depression [32], and in maintenance treatments [33–35]. For instance, a systematic review of computer-based interventions for depression found a mean effect size of *d* = 0.78 for the reduction of depressive symptoms post-treatment [34]. A recent review showed how face-to-face psychotherapy and internet-delivered therapy had similar effects [36].

Internet-interventions for depression are available in many languages. Research from Spanish language versions including López-del-Hoyo, Olivan [37] and Montero-Marín, Araya [38] reported positively on the effectiveness of a CBT-based internet-delivered programme for depression. A recent four-year descriptive, naturalistic study monitoring a web-based CBT treatment developed and researched in Mexico indicated that the intervention was useful for depressive symptoms [39]. A feasibility study in Chile found an online treatment to be beneficial, acceptable and feasible [40].

For the most part, internet interventions for depression have been researched in high-income countries. A recent systematic review found that only three articles reported results of RCTs on internet-delivered interventions for mental health conditions in LMICs [13].

### SilverCloud platform evidence: Space from depression

*Space from Depression (Yo puedo sentirme bien – Spanish version)* is a seven module CBT-based intervention for the treatment of depression. Recently, Richards, Timulak [41] reported that *Space from Depression programme* showed lower levels of depression symptoms post-treatment, compared to their baseline score, yielding a large post-treatment effect (*d* = 0.91). They reported significant differences between the treatment group and waiting list control group (*d* = 0.50). The positive outcomes were maintained at three and six months’ follow-up. The treatment was evaluated by users as acceptable and satisfactory [42].

### Culturally adapted psychotherapy (CAP)

Although low-intensity interventions for depression have been developed in western high-income countries and these interventions therefore have been influenced by their specific cultural context (for example, Ireland, UK, Australia), it is important to consider how cultural context may impact on the adaptation for use in LMICs such as Colombia. The authors argue that cultural aspects need to be taken into consideration when translating and adapting interventions to help guarantee similar results to those that have been achieved in high-income countries.

Culturally adapted psychotherapy (CAP) is defined as a systematic change of intervention protocols through consideration of relevance to the culture of the target population and modifies treatment in accordance with clients’ contexts and values [43]. According to Resnicow, Soler [44] cultural sensitivity has two dimensions, top-down adaptations (e.g., language) and bottom-up adaptations (e.g., cultural, social, historical, environmental and psychological aspects), which indicate varying degrees of integration of culture in psychotherapy. Additionally, ecological validity refers to a process that allows generalisation of assumptions derived from research situations to other environments and considers dimensions such as language, persons, metaphors, concepts, contexts, methods, and goals [45]. Further, principles from cross-cultural assessment research (i.e., functional equivalence, conceptual equivalence, linguistic equivalence) contribute to assessing the cultural adaptation of the programme [46].

### Outcomes from CAP research

Meta-analyses have analysed the efficacy of CAP in comparison to non-adapted interventions and other control groups such as waiting list groups in adults. A recent meta-analysis found 136 published studies from previous meta-analysis. The meta-analysis found the overall affect size was *d* = 0.67, which indicates that culturally adapted interventions have better outcomes than other conditions (non-adapted treatment or control group). Likewise treatment effect sizes were significantly larger (*d* = 0.76) in treatment studies than in prevention studies (0.25) [47].

An older meta-analysis by Griner and Smith [48] reported the outcomes from 76 studies of service providers that were classified according to ethnic and/or socio-racial status. The results showed a weighted average effect size of (*d* = 0.45), indicating a moderately strong benefit for the culturally adapted interventions in comparison to control group.

### Culturally adapted internet-delivered treatment

Some studies have considered cultural adaptation for low-intensity internet-delivered treatments. An open trial study [49] examined the preliminary efficacy and acceptability of a culturally modified therapist-guided CBT treatment for anxiety and depression. The results showed that participants improved significantly across all outcome measures, with large within-group effect sizes (Cohen’s *d*) at post-treatment (*d* = 1.08 to 1.74) and 3-month follow-up (*d* = 1.53 to 2.00). Another study [50] showed the efficacy of a cognitive behavioural internet-delivered treatment for depression with weekly telephone support. Treatment group participants reported significantly reduced depressive symptoms (Cohen’s *d* = 0.93) up to 3-months after treatment compared to a control group. Furthermore, Ince, Cuijpers [51] in a randomised control trial demonstrated reductions in depression symptoms in participants using the internet-based, self-help problem-solving intervention, yielding a moderate effect size (Cohen’s *d* = 0.50). Finally, Wagner, Schulz [52] evaluated an internet-based CBT with therapist support for people with posttraumatic stress disorder (PTSD), which showed significant decreases in symptoms of PTSD (*d* = 1.57), depression (*d* = 1.51), and anxiety (*d* = 1.50) and increases in quality of life (*d* = 1.17) post-treatment.

A recent review and meta-analysis on cultural adaptation of minimally guided interventions for common mental disorders, which included e-mental health delivered interventions and bibliotherapy, found that insufficient details on the methodologies used for cultural adaptation were reported. However, these studies showed an increase in effect size of 0.117 (*P* = .04), or a 14% rise in pooled efficacy [53]. Despite the outcomes showing positive post-treatment results, more research is required to develop interventions that incorporate systematic CAP frameworks, especially as the processes for culturally adapting interventions have not been systematic and clearly or fully described in previous research. The current study seeks to examine the acceptability and efficacy of a culturally adapted cognitive behavioural internet-delivered intervention in Colombia - South America.

## Method

### Aims and hypothesis

We aim to assess the efficacy of a culturally adapted cognitive behavioural internet-delivered treatment for college students with depressive symptoms in Colombia. In line with other studies in high-income countries (HICs), and using an already established intervention, we hypothesise that the culturally adapted *Space from Depression* programme will be efficacious, with significant changes within the treatment group and differences post-treatment between the active treatment and the waiting list control group.

#### Overview

The study is a mixed method approach utilising in study 1 quantitative and qualitative methods to assist in the cultural adaptation of the *Space from Depression* intervention and in study 2 a randomised control design to examine the efficacy of the culturally-adapted intervention.

#### Procedure

The programme *Space from Depression* will be culturally adapted for a Colombian population using cultural sensitivity and ecological validity frameworks, including principles from cross-cultural assessment research (Study 1). Once the programme is culturally adapted, it will be tested using a randomised controlled trial methodology (Study 2).

#### Study 1: Cultural adaptation (cultural sensitivity and ecological validity)

The process for *cultural sensitivity* will be developed using a “*top-down”* methodology as described in the framework by Resnicow, Soler [44]. This process will be carried out by the principal researcher [name] in conjunction with collaborators from SilverCloud Health (the developers), and professional translators and video production teams from Colombia. The process will involve a revision of the translated content in all sections and the inclusion of Colombian expressions for instance, “*guayabo*” (hung over), “*ciclovía*” (bike roads on Sundays) among others. Furthermore, videos and personal stories will be revised to include typical situations and stereotypes for Colombian students, such as Colombian actors and Latin American college stories (e.g. economic problems, pregnancy, relationships).

The process for *ecological validity* will be developed using approaches proposed by Bernal and Sáez-Santiago [45] and Helms [46] and will involve an evaluation of the programme by Colombian users and clinical experts. Through the use of a robust and theoretically-based methodology, the goal is to arrive at an acceptable and culturally adapted intervention that can then be used in a trial to examine its efficacy.

#### Participants

Five student users from a university in Colombia will evaluate the programme. Five experts in clinical psychology from Colombia and two clinical psychology experts from Argentina and Spain, who have experience with internet-delivered interventions and with translation and adaptation of interventions for use in Latin America, will evaluate the programme using the Cultural Relevance Questionnaire (CRQ) that was developed for this study.

#### Eligibility criteria

Students will be selected on the following criteria: a) clinical psychology masters and PhD students at a Colombian University. Experts will be selected on the following criteria: a) native Spanish speaker from Colombia and other Spanish speaking countries; b) PhD in clinical psychology or in psychology; and c) experience in: CBT, depression, research, and low-intensity internet-delivered treatment. These criteria guarantee the rigorousness of the culturally adapted programme.

#### Recruitment and procedure

An email will be sent to masters and PhD psychology students with information about the research study, its aims and a description of the task. Thereafter, they will attend an information session with the researcher [name] to further explain the study and to collect the informed consent documents from the participants. Participants will then review the programme and complete the CRQ after engaging with all of the treatment modules.

An invitation email will be sent to the seven identified expert researcher/ clinical psychologists in Bogota, Argentina and Spain. They will receive the study information, aims of the research and why it is important, and an invitation to evaluate the *Space from Depression* (*Yo puedo sentirme bien*) programme using the Cultural Relevance Questionnaire. Once they have signed the informed consent document and returned it by email to the research team, they will receive access to the platform and review the programme.

#### Study 2: Efficacy trial

The implementation of the culturally adapted programme and its evaluation among students using a randomised controlled trial methodology at two sites in Colombia.

### Sample size

Power analysis, carried out in G-Power using significance level α = 0.05 and power = 0.80 determined 45 subjects would be required for each test condition (active group and waiting list) to observe a moderate effect (*d* = 0.50) post-treatment between groups [54].

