#### Study 2: Efficacy trial

All analyses will be based on the intention-to-treat principle. Participants’ data will be included irrespective of treatment compliance. All of the data will be prepared and reviewed in SPSS.

Descriptive statistics will be used to analyse sociodemographic variables (e.g., gender and age). Chi-squared and t-tests will be used to examine demographic differences and clinical characteristics in the groups [67].

Effects will be tested at the 0.05 level. To assess significant changes over time, repeated measures ANOVAs will be performed for the primary outcome measure for depression (PHQ-9) and secondary outcome (GAD-7) [68]. The magnitude of effects within and between the two groups will be established by Cohen’s *d* statistic [67]. This will determine what is considered a small effect (*d* ≥ 0.2), a medium effect (*d* ≥ 0.5) and a large effect (*d* ≥ 0.8) [69].

Analyses will be carried out with participants who have clinically significant changes at the end of the intervention and at follow-up. The assessments will be made using pre-treatment scores, and these will be compared to post-treatment scores and follow-up scores on the outcome measures PHQ-9 and GAD-7. The analysis will be based on the Jacobson & Truax method, where a reliable change equals the difference pre-test and post-test, divided by the standard error of the difference [70].

Linear Mixed Model will be used for repeated measures (PHQ-9, GAD7) on each participant over time; it allows for a variety of correlation patterns (variance and covariance structures) to be explicitly modelled [71]. Also, it allows the measures on each subject to be used while accounting for missing data.

Participants’ responses in the HAT, identifying helpful and non-helpful events in the therapy and their impacts will be analysed qualitatively [66]. At the beginning, individual units of text will be analysed and identified out of their context. Next, these meaning units will be organised into helpful and non-helpful events and their impacts. Finally, these will be grouped into categories, which will be suitably named and defined.

Descriptive analysis will be used to analyse quantitative data from the SAT and their qualitative responses analysed using thematic analysis.

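### Forty-five per arm does not give 80% power for d = 0.50 post-treatment: a two-sided two-sample test has about 65%, before any drop-out

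*Protocol article*

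**What the plan says.** The Sample size section of the protocol article describes a calculation in G-Power "using significance level α = 0.05 and power = 0.80". It reports that this calculation "determined 45 subjects would be required for each test condition (active group and waiting list) to observe a moderate effect", which makes 90 in total, and it sets the target as "to observe a moderate effect (*d* = 0.50) post-treatment between groups". It does not name the test, the sidedness, a correlation between occasions or an allowance for losses.

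The planned analysis for Study 2 says only "Effects will be tested at the 0.05 level", again without sidedness. It says that "repeated measures ANOVAs will be performed for the primary outcome measure for depression (PHQ-9") and for the GAD-7, and it also names a linear mixed model, on the ground that "it allows the measures on each subject to be used while accounting for missing data". No correlation or attrition rate appears there either.

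The target effect has a source. The section on evidence for the platform reports a between-group d of 0.50 against waiting list in an earlier trial of the same programme.

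**The concern.** The section gives software, alpha, power, effect size, contrast and result, so the result can be checked against its own inputs. A difference between two independent groups at one time point, expressed as Cohen's d, is a two-independent-means calculation. The familiar answer for d = 0.50 at 80% power is well above 45 per arm.

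The value 0.50 is the effect that the earlier trial of this programme found, and the Discussion expects similar results here. If 45 per arm is too few for that effect, the trial is short of power for the result it expects, while the article says otherwise. A non-significant result would then be read against a claimed 80% power that the stated comparison does not have.

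**Working it through.** **Inputs.** From Sample size: alpha 0.05, target power 0.80, d = 0.50 (so SD = 1), n = 45 per arm, equal allocation. Sidedness is not given, so both are tried.

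**Formula.** For two independent means with n per arm, the t statistic has 2n − 2 degrees of freedom and noncentrality d·√(n/2). Power is the probability that this noncentral t exceeds the critical value.

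**1. Trying to reproduce 45**

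| Test | n per arm for 80% power | Power at 45 per arm | Smallest d with 80% power at 45 |
|---|---|---|---|
| Two-sided | 64 (0.795 at 63; 0.801 at 64) | 0.650 | 0.60 |
| One-sided | 51 (0.799 at 50; 0.806 at 51) | 0.761 | 0.53 |

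At n = 45 the noncentrality is 0.50 × √22.5 = 2.37. The critical value on 88 degrees of freedom is 1.99 two-sided or 1.66 one-sided. The normal approximation gives 63 and 50 per arm, and power of 0.66 and 0.77 at 45, so the gap is not rounding. Forty-five is the two-sided answer for d = 0.60 (power 0.795 at 44, 0.804 at 45).

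**2. Using the baseline measurement.** With correlation r between baseline and week 7, the effective d is 0.50/√(1 − r²) for covariate adjustment and 0.50/√(2(1 − r)) for a change score. A two-occasion group-by-time test in a repeated-measures ANOVA is the change-score test.

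| Analysis, 45 per arm, two-sided | r | Effective d | Power |
|---|---|---|---|
| Baseline-adjusted | 0.30 | 0.524 | 0.69 |
| | 0.40 | 0.546 | 0.73 |
| | 0.50 | 0.577 | 0.77 |
| | 0.55 | 0.599 | 0.80 |
| | 0.60 | 0.625 | 0.83 |
| Change score | 0.50 | 0.500 | 0.65 |
| | 0.60 | 0.559 | 0.75 |
| | 0.65 | 0.598 | 0.80 |

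**3. The repeated-measures between-factor option.** With f = d/2 = 0.25, m occasions, correlation ρ and total N, the noncentrality is f²·N·m/(1 + (m − 1)ρ). The total N for 80% power is:

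- 2 occasions: 90 at ρ = 0.4 and 98 at ρ = 0.5.
- 3 occasions: 86 at ρ = 0.5 and 96 at ρ = 0.6.

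So 45 per arm does appear, for example at 2 occasions and ρ = 0.4: 0.0625 × 90 × 2/1.4 = 8.04, power 0.80. But this test takes d = 0.50 as the group difference averaged over occasions, baseline included. Randomisation makes the expected baseline difference zero, so a week-7 difference of 0.50 averages to (0 + 0.50)/2 = 0.25. The mean of two occasions has variance (1 + 0.4)/2 = 0.7, the effective d is 0.25/√0.7 = 0.30, and power at 45 per arm is 0.29.

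**4. Losses by week 7.** The article gives no rate, so these are assumptions. The figures are for an unadjusted two-sided comparison of those observed.

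| Assumed loss | Analysed per arm | Power for d = 0.50 |
|---|---|---|
| 0% | 45 | 0.65 |
| 10% | 40.5 | 0.60 |
| 20% | 36 | 0.55 |
| 30% | 31.5 | 0.50 |
| 40% | 27 | 0.44 |

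**The case against.** The strongest reply is that the article never names a t-test. The planned analyses are repeated-measures ANOVA and a mixed model, and G-Power's repeated-measures between-factor option returns exactly 90 in total for plausible settings. On this view the article left out a test family and a correlation and did not miscalculate, and 65% is not the power of the analysis that will be run.

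Part of this stands. The 65% belongs to an unadjusted two-sided comparison and should be labelled so. An analysis that uses the baseline PHQ-9 could do better, reaching 0.77 at a correlation of 0.5 and 0.80 at 0.55 with covariate adjustment.

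The rest does not rescue the statement. The option that returns 90 sizes an effect averaged over baseline, which is not the post-treatment contrast that the section names; for that contrast its power is lower, not higher. The other routes to 45 need a correlation of about 0.55 or 0.65 that the document does not state. Nor can a high value be presumed, since eligibility restricts baseline PHQ-9 to 10–19 and range restriction generally lowers such a correlation.

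On losses, the reply is fair that the rates above are assumed, that the Procedure section plans emails and telephone calls to recover measures, and that the mixed model uses all available data. A condensed article may also leave an inflation factor to the full protocol. Attrition is therefore a secondary point. The shortfall exists with complete data.

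**Conclusion.** The concern holds. From the inputs given, 45 per arm is not the sample size for 80% power under either sidedness: the requirement is 64 two-sided or 51 one-sided. With complete data and an unadjusted two-sided test, power for d = 0.50 is 0.65, so a true effect of that size would be missed about one time in three. The smallest effect with 80% power is d = 0.60.

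These figures assume independent groups, equal allocation and 45 analysed per arm. Baseline adjustment would close the gap only with a correlation of about 0.55 or more. If 30% were lost by week 7, an assumed rate, the unadjusted test would have about an even chance of detecting d = 0.50.

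**What to change.** Rewrite the Sample size paragraph in one of two ways:

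- State that 45 per arm gives 65% power for d = 0.50, and 80% for d = 0.60, with a two-sided two-sample test at alpha 0.05.
- Base the calculation on a baseline-adjusted week-7 comparison of PHQ-9, state the assumed baseline to week-7 correlation and its source, and report the resulting power. The claim of 80% for d = 0.50 with 45 analysed per arm can stay only if a correlation of about 0.55 or more can be justified.

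In both cases state the sidedness, and add the power at the number expected to be analysed at week 7, with the assumed loss stated.

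The cost is one paragraph. No extra enrolment and no change to conduct is needed for this correction; recruitment began in August 2016. The price is a less favourable power statement, against which a non-significant result can be read fairly.
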